**POP-Q:**

| Aa = | Ba = | C = |
| --- | --- | --- |
| Gh = | Pb = | TVL = |
| Ap = | Bp = | D = |

Otoottote doycho sentimetirenni wori! __________________________

Uurrite bussanni hedhenanni bikkinonni bikko: □ nose □ dinose qelpheepho(mL):______

**Gafa-X: Otootto Gobbara Fulturo Hiittoo Heshshote Gade Nooro Bunxanni Borri- Xa’mo (Otootto Gobbara Fultino Amuwira Calla)**

**Hajajo**: Konni woroonni noo malaati leellannohu otootto gobbara higge fultino amuwira leellanno malaateeti. Taaltino dawarora malaatisi.

| **Amado** | **Xa’muwa** | 0  Lowo geeshsha danchaho | 1  danchaho | 2  duushshanno | 3  diduushshanno | 4 lowo geeshsha didushshanno |
| --- | --- | --- | --- | --- | --- | --- |
| XAPHOOMU FAYYIMMA(GHP) | Fayyimmakki hiittoonni xawisatta? |  |  |  |  |  |
|  |  | **0 wo’ma woyte dikkino** | **1 shiima yanna** | **2 mereerimunni** | **3 lowo geeshsha** |  |
|  | Otootto gobbara higge fulate mitiimma heeshshokkira. |  |  |  |  |  |
| MINI LOOSO LOOSA HOOGA HOGGAolhlimitations | Otootto gobba higge fultinohe dafira, mini loosi hittoo mitiimma abbinohe? |  |  |  |  |  |
|  | Otootto gobba higge fula ,mini gobbayidi loosikkira mitiimma abbinohe? |  |  |  |  |  |
| Mannu noowa ha’ra hoogate qarra | Otootto gobba higge fulte milli yaattata mitiinsinoheni? |  |  |  |  |  |
|  | Otootto gobbara higge fultannohe baychunni baycho hodhate mitii’mitanni? |  |  |  |  |  |
|  | Otootto gobba higge fultino daafira,dagoomu ledo xaadate mitii’mitta? |  |  |  |  |  |
|  | Otootto gobba higge fultinohe daafira miillaki ledo xaadate mitii’mitta? |  |  |  |  |  |
| Mannu ledo gade ledo | Otootto gobba higge fultinohe daafira,maatekkira mitiimma abbinoheni? |  |  |  |  |  |
|  | Otootto gobba higge fultino daafira siimu xaadooshshira mitiimma abbinohe? |  |  |  |  |  |
|  | Otootto gobba higge fultino daafira,maatekkira mitiimma abbinohe? |  |  |  |  |  |
| Akata | Otootto gobba higge fultino daafira,dadillu macciishshamannoheni? |  |  |  |  |  |
|  | Otootto gobbara higge fultino daafira caaccawaatani? |  |  |  |  |  |
|  | Otootto gobba higge fultino daafira ate bunshe macciishshantannoheni? |  |  |  |  |  |
| Goxichu/wolqa | Otootto gobba higge fultino daafira goxatta woyte mitii’mitta? |  |  |  |  |  |
|  | Otootto gobba higge fultinohe daafira bunshe calla macciishshantannohe? |  |  |  |  |  |
| Marichi qaafo adhita?taken | Hocoota/pade horonsiraata. |  |  |  |  |  |
|  | Otootto gobba higge fultanno yannara xiibbe egennootta? |  |  |  |  |  |
|  | Otootto gobba higge fultino daafira xisso/injaa hooga maciishshantanoheni? |  |  |  |  |  |
|  | Otootto gobba higge fultinohe daafira uurrate mitii’mattani? |  |  |  |  |  |
| **Kalqete Dhiwamaasinetenni Afi’nanni Babbaxxitino Borri-Xa’mo**  Konni woroonni no borri-xa’mo xa’minannihu goofimarchohooti. Xa’minannihu dhibbu malaati nooriranna nookkihuraati. Xa’minanni yanna lewu(6) agani gedensaanniiti | | | | | |  |
| **Kalqete Dhiwamaasinetenni Afi’nanni Babbaxxitino Borri-Xa’mo** | Mamoote way shuma ciphi yitannohehu? (taltino dawaaro dori) | 1= lowo geeshsha huroomma  2= woyyate  3= dhibbu ajanni ha’rinoe  4 = mitte soorro dino  5= shiima geeshsha xissanni nooe  6= xissanni nooe  7= lowo geeshsha xissanni nooe | | | |  |

# **ANNEX-IV: Lifestyle Counselling and Pelvic Floor Muscle Training Protocol**

**What is a pelvic organ prolapse and what are the symptoms?**

Pelvic organ prolapse, often known as 'prolapse,' is a vaginal alteration in which a pelvic organ, such as the bladder, bowel, rectum, or uterus, slips downwards in the vagina, creating the sensation of "something coming down" or "vaginal heaviness." The protrusion might be felt on either the inside or outside of the vaginal wall. Bladder, bowel, and sexual issues can all be caused by prolapse. The pelvic organs - the bladder, vagina, uterus, and rectum - are held and maintained inside the bony pelvis by ligaments and muscles, which are collectively known as the "pelvic floor.”

To prevent incontinence, the pelvic floor muscles support the pelvic organs and manage the bladder and bowel. The pelvic organs can bulge into the vagina, forcing the vaginal walls to slip downwards, resulting in a prolapse, if either the pelvic floor muscles or the supporting structures fail. A prolapse might be minor, providing little or no discomfort, or severe, causing several issues and negatively impacting your quality of life. Whether the downward bulge is felt or visible within the vagina or can be felt or seen outside the vaginal entrance may affect how much the prolapse interferes with your life. Prolapse might vary from day to day and even within a single day. On some days, you may be completely unaware of your symptoms, while on others, you may be acutely conscious of them; it may be alright in the morning but very uncomfortable later in the day. The sensation of’ something coming down' or of vaginal heaviness/bulge is the most typical symptom. Other common bladder and bowel symptoms can be caused by a prolapse, but they may also be unrelated.

**What causes pelvic organ prolapse?**

Prolapse is caused by a number of events that disrupt the vaginal support system. The factors linked to pelvic organ prolapse are mentioned below, along with a brief explanation of why they are linked.

**Pregnancy and childbirth**: This is the most prevalent cause, especially if the delivery was vaginal. The growing baby puts pressure on the pelvic organs and pelvic floor muscles, while hormonal changes through pregnancy lead the supporting ligaments to relax in preparation for birth. An episiotomy, a vaginal tear, or a forceps assisted delivery can weaken the supporting system, resulting in complications at the moment of delivery or later in life. Pelvic floor muscle workouts can help you maintain the strength of your pelvic floor muscles while you're pregnant.

**Obesity and being overweight**: the more weight your body has to manage, the more pressure is exerted on the pelvic organs and through the pelvis. A significant weight gain might place additional strain on the supporting structures, increasing the risk of prolapse.

**Heavy lifting**: If your day-to-day activities include heavy lifting or frequent bending, the increased abdominal pressure pushing downwards may raise the risk of a prolapse, especially if your pelvic floor supports are in sufficient.

**Family history**: A strong family history of pelvic organ prolapse, such as your mother or sister, may enhance your chances of developing a prolapse. This is assumed to be owing to a weak collagen type.

**Age**: As you get older, you're more likely to get a prolapse. Muscle strength may deteriorate as a result of aging, along with other changes.

**Menopausal changes**: As your levels of vaginal estrogen drop, some of the hormonal change that accompany menopause might exacerbate prolapse symptoms. The reduced amount of vaginal estrogen after menopause may impact prolapse symptoms.

**Constipation**: constipation and straining to empty your bowels might increase the risk of prolapse or worsen the existing prolapse. Increased intra-abdominal pressure is directed down onto the pelvic floor, causing strain and tension.

**Chronic cough:** If you have asthma or other illnesses that cause you to cough frequently, you may be at risk for a prolapse. This is caused to the pelvic floor being strained by recurrent increases in intra-abdominal pressure.

**Previous pelvic surgery**: If you've already had a prolapse repair or a hysterectomy, your chance of getting another prolapse are higher.

**What can you do to help a pelvic organ prolapse?**

Pelvic organ prolapse is not a life-threatening disorder, and not all prolapses deteriorate; in fact, some may improve. If you have been told you have a pelvic organ prolapse, you might want to consider the following options:

• Do nothing and wait for your symptoms to improve.

• Develop healthy bladder and bowel habits

• Change your lifestyle to lessen downward pressures in your pelvis, especially if any of your current activities aggravate your symptoms, such as weight reduction or avoiding or reducing the amount of lifting you do.

• Increase the vaginal support by strengthening your pelvic floor muscles.

• Consult a gynecologist about surgery as a possibility (or choice).

If your prolapse is not bothersome, you may decide to do nothing. However, research suggests that completing pelvic floor muscle exercises and following the recommendations below can help prevent your prolapse from worsening.

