## Description of Intervention

From each selected health facility, two female Nurses or Midwives will be trained on Pelvic Floor Muscle Training and how to counsel patients. The training will be given for nurses and midwives by urogynaecologist. The training will have a theory, simulation, and video aids.

Among women diagnosed to have symptomatic stage I-III pelvic organ prolapse, 136 will be assigned to the interventional and control groups based on their pre-assigned enumeration area (cluster). Those assigned to intervention will receive pelvic floor muscle training and prolapse lifestyle advice focusing on constipation, chronic coughing, heavy lifting, and other medical conditions. The control group will receive only lifestyle modification but not trained on pelvic floor muscle exercise. The detailed counselling will be provided using a translated Sidaamu Afoo version of a leaflet (Annex-IV) (22).

In the interventional group, at the initial visit, women will be informed about their stage of POP, type of prolapse (anterior, posterior, or central), the advantage of pelvic floor muscle exercise, and how it works. The detail of the exercise and follow-up schedule will be explained in detail in a private room for 30-40minutes. They will be trained to sit or lie comfortably, train pelvic muscles with 10 times 10-second maximum holds, and 10 fast contractions. This will be repeated at least three times per day (morning, afternoon, and night) (14, 22). They will be invited to attend five visits (at weeks 0, 2, 6, 10, and 15) at a nearby health facility. Five visits are preferred because 15-weeks intensive training is recommended to get adequate muscle strength) (23).

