**Taking steps to lower your intra-abdominal pressure**

**Reduce your cough:** If you have a chronic cough, make sure you take medications as directed and drinking plenty of water.

**Lifting**: It is not just the weight of the object you are lifting that can aggravate your symptoms. Bending and lifting on a regular or recurrent basis might also be a concern.

• Develop a good lifting habit for all chores, including light ones. Before each lift, tighten your   pelvic floor muscles.

• Splitting weights for carrying, making more frequent journeys, and lifting correctly when taking something from low down are all good ideas.

**Exercise and activities**: Avoid activities that aggravate symptoms, like prolonged standing.

Whenever feasible, try to divide your day into shorter intervals of standing with moments of sitting in between. Jumping, jogging, or aerobics (any activity that requires both feet to be off the ground at the same might aggravate your symptoms, especially if your pelvic muscles are weak.  Weight-bearing activities might sometimes put too much downward pressure on the body. Low-impact exercise like modified aerobics, cycling, a cross trainer, quick walking can be substituted.

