**INSTRUCTIONS: THE FOLLOWING PIECE OF COUNSELING IS ONLY FOR WOMEN WHO ARE PART OF THE INTERVENTIONAL CLUSTERS.**

**Increasing the strength of your pelvic floor muscles**

To support the pelvic organs, the pelvic floor muscles operate as a hammock. PFM exercise will strengthen and retain the muscles to be more effective at supporting the pelvic organs, reducing prolapse symptoms. Pelvic floor muscle exercises (should comprise both long, held squeezes and brief, rapid squeeze, with each squeeze ending with complete relaxation of muscles. To assist the muscles get stronger and more effective, you should work them until they tire and repeat the exercise on a regular basis.

These exercises can be done in any position, however if your prolapse extends beyond the vaginal opening, you may find it easier to do them lying down.  If your prolapse isn't too bad, you might be able to complete these exercises while sitting. Inside, you should feel a squeeze and lift. Avoid holding your breath or squeezing other muscles like your legs or buttocks.

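### The English Annex-IV conflicts with the control-arm definition on what control women are told about pelvic floor exercise, and the Sidaamu Afoo version appears to say something different again

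*Protocol*

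**What the plan says.** Paper-III, Description of Intervention, sets the comparator: "The control group will receive only lifestyle modification but not trained on pelvic floor muscle exercise". Lifestyle advice is described there as covering constipation, chronic cough, heavy lifting and other medical conditions. The same section names the vehicle: "The detailed counselling will be provided using a translated Sidaamu Afoo version of a leaflet (Annex-IV".

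The English Annex-IV contains one instruction that separates the arms, placed just before its exercise section: "THE FOLLOWING PIECE OF COUNSELING IS ONLY FOR WOMEN WHO ARE PART OF THE INTERVENTIONAL CLUSTERS". By its wording it restricts only what comes after it, so everything above it is for both arms. That shared text includes:

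- under What can you do to help a pelvic organ prolapse?, an option list with "Increase the vaginal support by strengthening your pelvic floor muscles", and then the statement that "research suggests that completing pelvic floor muscle exercises and following the recommendations below can help prevent your prolapse from worsening";
- under Taking steps to lower your intra-abdominal pressure, the lifting advice "Before each lift, tighten your" "pelvic floor muscles".

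The Sidaamu Afoo version of Annex-IV is printed after the English one and is shorter. It has its own restriction line ahead of its exercise section.

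Contamination is addressed in Randomization and in Data Quality Control. In both places the safeguard is a buffer of at least one kebele between intervention and control clusters.

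**The concern.** The trial compares lifestyle advice plus exercise training with lifestyle advice alone. Shared counselling text that recommends the exercise, or prompts a contraction, moves the control condition towards the intervention. Control women who act on it would shrink the difference in symptom change and bias the result towards no effect. It would also be less clear what the trial has compared.

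A geographic buffer limits the spread of information between villages. It cannot limit information that the trial's own counselling gives to control women.

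There are two possible routes: the leaflet and the nurses' spoken counselling. On the second, Description of Intervention has two nurses or midwives from each selected health facility trained both in the exercise and in counselling, and it does not confine this to intervention facilities. The adherence checks described run through the muscle trainer and the diary, so as written they would not show exercise taken up by control women.

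**Working it through.** **1. The texts side by side**

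| Content | Description of Intervention (control) | English Annex-IV, above its marker | Sidaamu Afoo Annex-IV, above its marker |
|---|---|---|---|
| Exercise said to help prevent worsening | Not part of the control condition | Present | No counterpart seen |
| Strengthening listed as an option | Not part of the control condition | Present | No counterpart seen |
| Tighten the muscles before each lift | Heavy lifting is covered; no contraction mentioned | Present | No counterpart seen |
| Exercise regimen | Controls not trained | Absent; below the marker only | Absent; below the marker only |

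The last column rests on structure and repeated terms, not on a translation. The what-to-do section has three bullets, which match the English bowel advice. The lifting section is brief. The term for the exercise (*Halli wori mannimmate guunte*) first appears after the restriction line. A speaker should confirm this reading.

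**2. The plan's sample size, reproduced**

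Inputs from Paper-III, Sample Size Determination: changes of 3.16 (SD 4.78) and 0.12 (SD 3.86), 99% confidence, 80% power, 16% loss.

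- Difference: 3.16 − 0.12 = 3.04.
- Common SD: √((4.78² + 3.86²)/2) = 4.344.
- n per arm = 2 × (4.344 × (2.576 + 0.842)/3.04)² = 47.7, so 48 per arm and 96 in total.
- After loss: 2 × 47.7/0.84 = 113.6, against 113.4 stated.
- After the stated inflation factor: 113.4 × 1.35 = 153.1, against 155 stated.

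The plan's figures reproduce closely. None of them is disputed here.

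**3. Illustration of dilution**

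Let f be the share of control women who take up exercise and gain the full planned benefit. The documents give no value for f. The 48 per arm is the number before inflation for loss and clustering, used as the equivalent number of independent observations. Alpha is 0.0125, from Data Management and Analysis.

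- Difference = 3.04 × (1 − f).
- Standard error = 4.344 × √(2/48) = 0.887.
- Power = Φ(difference/0.887 − 2.498).

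| f | Difference | Power |
|---|---|---|
| 0% | 3.04 | 82% |
| 10% | 2.74 | 72% |
| 20% | 2.43 | 60% |
| 30% | 2.13 | 46% |

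For f = 20%: 2.43/0.887 − 2.498 ≈ 0.245, and Φ(0.245) ≈ 0.60.

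At the alpha of 0.01 used for the sample size, the four powers are 80%, 69%, 57% and 43%. If the control SD is also allowed to widen because the arm becomes a mixture, the last three rows at 0.0125 become 70%, 56% and 41%.

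**The case against.** The strongest reply is that the English lines may never reach a participant. Description of Intervention names the Sidaamu Afoo leaflet, that leaflet is already printed in the protocol, and its shared part appears to lack all three items. No passage gives the nurses an English script. This stands, and it limits what can be claimed about exposure. It does not remove the inconsistency. The working leaflet is called a translation of Annex-IV, yet the two versions do not appear to match. If the translation is brought into line with the English, the prompts enter the control arm. If it is not, the English annex misdescribes the comparator.

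A reader might infer that the leaflet does contaminate the control arm. The documents do not support that. Controls are described as not trained, and even the English shared text gives no regimen, diary or supervision. One sentence of encouragement, one item in a list and one lifting cue are a possible source of dilution, not demonstrated contamination.

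A reader might also add the line "Pelvic floor muscle workouts can help you maintain the strength of your pelvic floor muscles", which stands above the marker too. It concerns exercise during pregnancy. Trial women come from the Paper II survey, whose Study Population section excludes pregnant women, so it carries little weight.

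Finally, the power figures should not be read as a forecast. Uptake is an assumption. Giving untrained women the full benefit planned for a trained arm with five visits is the extreme case for any given uptake.

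**Conclusion.** The point holds as an inconsistency with a possible cost. The English Annex-IV conflicts with the control-arm definition, and the two language versions appear to differ above their restriction lines. As written, the protocol does not fix what control women are told about pelvic floor exercise.

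The risk is bias towards the null. Its size cannot be estimated from the documents. The fall from 82% to between 72% and 46% power holds only for 10% to 30% uptake with full benefit, 48 per arm, alpha 0.0125 and clustering ignored. It shows that the design has little room for dilution, not that dilution will occur. If a Sidaamu Afoo speaker confirms the omissions and the nurses keep to that leaflet, exposure may be small. The documents would still need to agree.

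**What to change.** Before counselling starts:

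- Reconcile the two English Annex-IV sections (What can you do to help a pelvic organ prolapse? and Taking steps to lower your intra-abdominal pressure), the Sidaamu Afoo leaflet and Description of Intervention, so that all of them agree on the text each arm receives.
- Have a Sidaamu Afoo speaker compare the two leaflets line by line, including the position and wording of the restriction line.
- Check any counselling script the nurses use against the reconciled text.

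Which advice control women should receive is a clinical matter for the investigators. The statistical requirement is only that the comparator be described in one way throughout. The cost is a text edit and a language check, with no added visits or staff.

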**Bowels**

- It's critical to avoid constipation since it puts additional strain on the pelvic floor muscles, which can exacerbate prolapse symptoms.
- Eating a healthy diet rich in fruits, vegetables, and fiber can assist.
- Make sure you're getting enough water as well (between 1.5 to 2 liters of fluid per day).

**When it's time to leave, try to adopt appropriate toilet habits**:

- - Don't overwork yourself
  - Sit fully on the toilet, rather than hovering; this will aid in the relaxation of the correct muscles.
  - Stand with your feet apart and your arms comfortably resting on your legs, supported by a seat or support.
  - Don't tighten your abdominals; maintain your tummy relaxed.
  - Avoid holding your breath; instead, aim to maintain a calm breathing pattern.
  - Sit fully on the toilet, rather than hovering; this will aid in the relaxation of the correct muscles.
  - Applying mild pressure vaginally on the bulging wall toward the rear canal may assist in more thoroughly and successfully emptying the bowels.

**Bladder**:

- Instead of going to the bathroom 'just in case,' go when your bladder needs to be emptied
- Sit fully on the toilet, rather than hovering; this will aid in the relaxation of the correct muscles.
- You might find it beneficial to lean forward and back numerous times after passing urine to help make sure that all the urine comes out
- do not push or strain to empty your bladder; you might increase the prolapse
- Try not to lower your daily fluids (1.5 – 2 liters per day is recommended); you may aggravate the prolapse if you push or strain to empty your bladder.
- The number of times you need to empty your bladder may not always be reduced by drinking less.

**Intercourse**

- Having sex with a prolapse is perfectly safe and will not harm or exacerbate the bulge.
- To aid with vaginal dryness or discomfort with penetration, consider alternative positions for sexual intercourse and use a suitable lubricant.

**Weight**:

- Being overweight causes the pelvic floor muscles to be overworked.
- If you reduce weight, your symptoms may improve.

**Taking steps to lower your intra-abdominal pressure**

**Reduce your cough:** If you have a chronic cough, make sure you take medications as directed and drinking plenty of water.

**Lifting**: It is not just the weight of the object you are lifting that can aggravate your symptoms. Bending and lifting on a regular or recurrent basis might also be a concern.

• Develop a good lifting habit for all chores, including light ones. Before each lift, tighten your   pelvic floor muscles.

• Splitting weights for carrying, making more frequent journeys, and lifting correctly when taking something from low down are all good ideas.

**Exercise and activities**: Avoid activities that aggravate symptoms, like prolonged standing.

Whenever feasible, try to divide your day into shorter intervals of standing with moments of sitting in between. Jumping, jogging, or aerobics (any activity that requires both feet to be off the ground at the same might aggravate your symptoms, especially if your pelvic muscles are weak.  Weight-bearing activities might sometimes put too much downward pressure on the body. Low-impact exercise like modified aerobics, cycling, a cross trainer, quick walking can be substituted.

